## Presentation of the drug

The under investigation product *T3^®^Solution for injection 10 μg/ml*is a clear, colorless solution.

*Composition of the Medicinal Product*

| **No** | **Name of ingredient(s)** | **Quantity / 1ml** |
| --- | --- | --- |
|  |  |  |
|  | **Active ingredient:** |  |
| 1. | Liothyronine sodium | 10.0μg |
|  | **Other ingredient (s):** |  |
| 1. | Dextran 70 | 60.0 mg |
| 2. | NaOH 1 N | q.s. pH 10 |
| 3. | Water for Injections | qs 1.0 |

*Proposed shelf life:* 1 month.

*Placebo:* Composition identical apart from the active substance.

## Known Drug reactions

### Oral Anticoagulants: T3 appears to increase catabolism of vitamin K-dependent clotting factors. If oral anticoagulants are also being given, compensatory increases in clotting factor synthesis are impaired. It is likely that a reduction in anticoagulant dosage may be required.

### Heparin: According to the literature, the action of heparin can be affected by T3 adminsitration. In the ThyRepair study, in patients with myocardial infarction receiving antiplatelet and anticoagulant therapies as gold-standard, serious adverse events such as hemorrhages or thrombosis were not observed. In patients in the ThySupport study, we advise to use unfractioned heparin and perform dose adjustment according to aPTT measurements.

### Insulin or Oral Hypoglycemics: Initiating T3 therapy may cause increases in insulin or oral hypoglycemic requirements. The effects seen are poorly understood. Patients receiving insulin or oral hypoglycemics should be closely watched during initiation of T3 therapy.

### Estrogen, Oral Contraceptives: Estrogens tend to increase serum thyroxine-binding globulin (TBG). Therefore, hypothyroid patients who are on thyroid replacement therapy may need to increase their thyroid dose if estrogens or estrogen-containing oral contraceptives are given.

### Tricyclic Antidepressants: Use of thyroid products with imipramine and other tricyclic antidepressants may increase receptor sensitivity and enhance antidepressant activity; transient cardiac arrhythmias have been observed. Thyroid hormone activity may also be enhanced.

### Digitalis: Thyroid preparations may potentiate the toxic effects of digitalis. Thyroid hormonal replacement increases metabolic rate, which requires an increase in digitalis dosage.

### Ketamine: When administered to patients on a thyroid preparation, this parenteral anesthetic may cause hypertension and tachycardia. Its use should be avoided.

### Vasopressors: Thyroid hormones increase the adrenergic effect of catecholamines such as epinephrine and norepinephrine. Therefore, patients receiving T3 may need lower doses of vasopressors.

## In the ThyRepair study, administration of T3 at the same therapeutic doses in patients with STEMI who received at the same time several other drugs (antiplatelets, anti-coagulants, β-blockers, ACE inhibitors,ARBs, aldosterone antagonists, statins, diuretics, insulin etc,) did not show any serious issue of drug reactions between T3 and other therapies.

## Drug storage and supply

The under investigation product and the placebo will be supplied by the Sponsor.

## *Proposed Storage conditions:* Store under 2-8^o^C.

**10.** **FLOW-CHART OF THE STUDY**

**General schedule for Patient and Investigator**

Patients with COVID19 pneumonia on mechanical ventilation or ECMO, n=90

Follow-up for 1 month, n=30

Follow-up for 1 month, n=30

Placebo group, n=30

T3 group, n=30

Randomisation 1:1, n=60

Assessment of eligibility, n=70

Signed inform consent, n=60

**11. STUDY PROCEDURES**

## Informed consent

The investigator must explain to each patient or legal representativethe nature of the study, its purpose, the procedures involved, the expected duration, the potential risks and benefits involved and any inconveniences it may cause.

Each patient or legal representative must be informed that participation in the study is voluntary, consent maybe withdrawn at any time and that withdrawal of consent will not affect subsequent medical treatment or relationship with the treating medical staff.

The Informed Consent Form should be administered by means of a standard statement, written in non-technical language. The patient or legal representative should have time to read and consider the statement before signing and dating it. Patient or legal representative should receive a copy of the signed document. No patient can enter the study before Informed Consent Form has been obtained.

## Screening evaluation

All patients diagnosed with COVID19 pulmonary infection receiving endotracheal [mechanical ventilation](https://www.sciencedirect.com/topics/medicine-and-dentistry/artificial-respiration" \o "Learn more about Artificial Respiration from ScienceDirect's AI-generated Topic Pages) or ECMO will be considered for enrolment in the study in the clinical sites. According to our plan, this study will need to screen approximately 90 patients, in order to enrol 60 patients that are eligible according to the inclusion and exclusion criteria and will provide signed informed consent.

Eligible patients with the above criteria will be approached and an informed consent will be asked from patients or relatives. After informed consent has been signed, each investigator has to inform the Chief Investigator within 24 hours about the new patient recruitment. Chief investigator is obliged to evaluate whether all criteria are met.

## Baseline data

All patients will have a full medical history taken and a clinical examination. The following are to be recorded:

- ***Patient profile*** (Height, Weight, gender, Race, Age and date of birth, Address and phone number, significant past medical history, smoking, time from onset of symptoms to admission)
- ***Any Co-morbidities***
- ***Medication at admission in ICU***
- ***Blood pressure and heart rate***
- ***Blood gases*** (pO2, pCO2, blood pH, lactate)
- ***Echocardiographic analysis***
- ***ECG***
- ***Standard Laboratory data:*** *Haemoglobin, White blood cells, platelets, urea, creatinine, glucose, CPK, LDH, AST, ALT, γ-GT, Total and Direct bilirubin, Albumin and total protein, INR, IL6, Procalcitonin, Ferritin, d-dimer,fibrinogen, electrolytes (Na, K, Ca, phosphate, Mg), troponin I, BNP, CRP, erythrocyte sedimentation rate*
- ***24h urine volume***

## Study assessments

***During stay in the ICU the following parameters will be recorded every 24 hours:*** Blood pressure, heart rate, oxygen saturation, temperature, blood gases, urine volume, need for inotropic support, standard medication, laboratory tests, ECG and evaluation of AEs.

**Echocardiographic analysis** will be performed every 48 hours during ICU stay

**Thyroid hormone levels** (Serum total T3, total T4 and TSH) will be determined at baseline and at 24h, 48h, 72h, and every 3 days till termination of drug administration or end of follow-up.

**Successful weaning** will be defined as no requirement for ventilatory support for 48 hours after extubation, or (in tracheostomised patients) discontinuation of ventilatory support or no need for ECMO support for 48 hours. The percentage of successfully weaned patients and the duration of required mechanical respiratory support or ECMO (in days) will be recorded.

**Individual adverse events** (AE) will be evaluated by the investigators and they will be reported to the sponsor. This includes the evaluation of seriousness, causality and expectedness and any relationship between the investigational medicinal product(s) and/or concomitant therapy and the adverse event. Adverse events will be recorded during 30 days follow-up. A 24h telephone line will be available for all patients in order to communicate with a study investigator and report any adverse event in the case of discharge from hospital.

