**Assessment of weaning from cardiorespiratory support**

- Successful weaning is defined as no requirement for ventilatory support after extubation (mechanical support) or support from ECMO for 48 hours. The primary objective will be measured as percentage of patients successfully weaned after 30 days of follow-up. The percentage of patients weaned at 20 days post-intubation will be a relevant secondary endpoint.

The ***secondary objectives*** of the study are:

1. **Assessment of hemodynamic status**

Hemodynamic status will be assessed by continuous blood pressure measurements (systolic, diastolic and mean BP) and the use of inotropic and vasoactive drugs.

1. **Assessment of pulmonary function**

Pulmonary function will be assessed by arterial measurement of blood gases, Horowitz-Index (pO2/FiO2) and lactate.

1. **Assessment of hepatic and renal function**

Hepatic and renal function will be assessed by laboratory measurements in blood and urine volume

1. **Assessment of cardiac function**

Echocardiographic assessment of systolic and diastolic function will be performed. Measurements of cardiac troponin-I will be used to assess myocardial injury

1. **Assessment of the course of** *COVID-19* **infection**

COVID-19infection will be assessed by inflammatory indices and their course (daily changes and absolute values) in blood (IL6, Procalcitonin, D-Dimers, Ferritin and CRP), temperature monitoring and time needed for the patient to become negative in COVID-19.

1. **Assessment of clinical outcome and safety**

Major events (*death, cardiac Arrest, electromechanical dissociation, pulmonary embolism, new myocardial infarction, stroke, pulmonary edema, cardiogenic shock and hypotension, septic shock, pulmonary embolism, serious bleeding*) and minor (*myocarditis, Venous Thromboembolism, left Ventricular mural thrombus, renal failure, hepatic failure, stress ulcers, minor bleeding,* [*paroxysmal supraventricular tachycardia*](http://emedicine.medscape.com/article/156670-overview)*and*[*atrial fibrillation*](http://emedicine.medscape.com/article/151066-overview)*, rythm disturbances*) will be recorded during the follow up period.

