**5.2 Echocardiography**

Echocardiographic assessment will be performed as part of the standard clinical care whilst the patients are still in hospital.

Images will be obtained using a 3.5 MHz transducer, at a depth of 12 to 20 cm in parasternal and apical views. Three cardiac cycles of the apical 4-, 3-, and 2-chamber views will be captured in 2D. Left ventricular volumes will be measured and the biplane Simpson’s rule will be applied.

Echocardiographic assessment of diastolic function (mitral E wave velocity/mitral annular velocity (E/E') ratio) and pulmonary congestion (PASP and IVC measurements) will be performed.

All echocardiographic data will be stored digitally and kept center for a centralized core lab reading. Two blinded expert operators will centrally assess data on a specific workstation.

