## 5.7 Recording and evaluation of laboratory and instrumental safety criteria

A number of laboratory measurements will be performed in blood samples in order to evaluate disturbances in blood cells, renal dysfunction, hepatic dysfunction and dysfunction in glucose homeostasis.

The following parameters will be measured Haemoglobin, white blood cells, platelets, urea, creatinine, Glucose, CPK, LDH, AST, ALT, γ-GT, Total and Direct bilirubin, Albumin and total protein, INR, fibrinogen, d-dimer, Electrolytes (Na, K, Ca, phosphate, Mg), Troponin I, BNP, urine volume.

12-leads ECG will be performed every day during ICU stay and every 2 days during hospital stay to assess basal heart rate and cardiac rhythm.

Pulmonary function will be assessed by regular measurements of blood gases (pO2, pCO2, blood pH,lactate).

The course of *COVID-19* infection will be assessed by regular temperature monitoring, inflammatory indices (white blood cells, CRP, IL6, Procalcitonin, Ferritin, D-Dimers) and positivity for active replication of *COVID-19.*

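### Most physiological, laboratory and inflammatory secondary measures have a dated schedule only in the ICU, so late between-arm comparisons depend on who has recovered enough to leave

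*Protocol*

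**What the plan says.** Section 11, Study assessments, introduces the list of vital signs, oxygenation, temperature, urine volume, inotrope need and laboratory tests with "During stay in the ICU the following parameters will be recorded every 24 hours". Echocardiography, in the same section, "will be performed every 48 hours during ICU stay". These measurements supply most of the secondary objectives in section 3: haemodynamic, pulmonary, hepatic and renal, cardiac, and inflammatory course.

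Other passages reach beyond the ICU:

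- Section 5.7: "12-leads ECG will be performed every day during ICU stay and every 2 days during hospital stay". It also foresees regular blood gases, temperature and COVID-19 positivity, but gives no days for them.
- Section 5.2: "Echocardiographic assessment will be performed as part of the standard clinical care whilst the patients are still in hospital". No frequency is given.
- Section 11, on adverse events: "Adverse events will be recorded during 30 days follow-up". Section 3 says that major and minor clinical events "will be recorded during the follow up period".
- Section 11, on thyroid hormones: "every 3 days till termination of drug administration or end of follow-up".

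Section 3 also lists "temperature monitoring and time needed for the patient to become negative in COVID-19". No section gives test days for it.

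Section 14 analyses serial measurements by repeated measures ANOVA. It expects no more than 5% missing per variable and proposes mixed-effects models for imputing repeated measurements, with best-case and worst-case sensitivity analyses.

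**The concern.** A patient who improves and moves to the ward may stop contributing dated values while alive, in hospital and within the 30-day follow-up. Improvement is the effect under test, so the loss is expected to differ by arm if the drug works. A comparison on, say, day 20 among patients still on the ICU schedule is then a comparison of two differently selected groups rather than of the randomised arms.

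At stake is the reading of the organ-function and inflammation results. A real benefit could look smaller than it is, and a marker that T3 leaves alone could look worse on T3. Values that were never recorded cannot be recovered by any later analysis plan, so this belongs in the protocol.

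**Working it through.** **Inputs.** Weaning at 30 days 15% (placebo) and 50% (T3), 30 patients per arm, two-sided alpha 0.05, 84% power: section 6. Missing data at most 5%: section 14. ICU mortality 81% to 97%: section 2. Not in the documents and therefore assumed: the time from weaning to ICU exit, the correlation r between a marker and recovery (0.3 to 0.7), and deaths by arm.

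**The plan's own figure.** Pooled normal approximation: mean proportion 0.325; SE under the null √(2 × 0.325 × 0.675 / 30) = 0.1209; SE under the alternative √((0.15 × 0.85 + 0.50 × 0.50) / 30) = 0.1122. Then (0.35 − 1.96 × 0.1209) / 0.1122 = 1.007, so power is 84.3%. The stated 84% is reproduced, and the schedule does not affect it.

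**How many could leave the schedule.** T3: 0.50 × 30 = 15. Placebo: 0.15 × 30 = 4.5. Together 19.5 of 60 = 32.5%. The 5% ceiling is 3 of 60. This is an upper bound for loss through weaning, because it supposes that every weaned patient has left the ICU by day 30.

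**Selection, deaths set aside.** Let latent severity be standard normal within each arm, with the least sick fraction p leaving. The mean of those remaining, measured from their own arm's mean, is φ(z_p) / (1 − p).

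- T3, p = 0.50: 0.3989 / 0.50 = 0.798.
- Placebo, p = 0.15: 0.2332 / 0.85 = 0.274.
- Difference: 0.524 SD.
- If only half of the weaned have left (p = 0.25 and 0.075): 0.424 − 0.153 = 0.271 SD.

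Two cases follow.

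1. *Marker unaffected by T3.* The apparent harm is r × 0.524, which is 0.16 SD at r = 0.3 and 0.37 SD at r = 0.7. With half departed it is r × 0.271, or 0.08 to 0.19 SD.
2. *T3 shifts severity itself.* Moving weaning from 15% to 50% across one common threshold needs a shift of z(0.50) − z(0.15) = 1.04 SD. On the common scale the remaining T3 patients average 0.80 − 1.04 = −0.24 and the remaining placebo patients +0.27. The visible difference is 0.51 SD instead of 1.04 SD, so about half the benefit disappears without reversing.

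**Adding deaths.** Suppose also that the sickest die first and that T3 does not change the latent scale. Over assumed deaths of 0 to 81% (placebo) and 0 to 40% (T3), the gap on the latent scale (T3 minus placebo, positive meaning T3 looks sicker) runs from −0.15 to +1.75 SD. Among the combinations tried it is negative only with no placebo deaths and 40% T3 deaths. At 81% placebo deaths, 30 × (1 − 0.81 − 0.15) = 1.2 placebo patients remain on the schedule at day 30, too few for a comparison.

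**The case against.** Section 11 sets a frequency within the ICU. It does not say that recording ends there, and section 5.7 foresees regular gases, temperature, inflammatory indices and COVID-19 positivity with no ICU limit. That is fair as far as it goes, but no days are attached, whereas the same section writes an explicit ward schedule for ECG. A site that follows the plan has no dated ward values to record.

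Section 14 offers mixed-effects models and sensitivity analyses. With daily values up to ICU exit, such models can recover part of the loss when exit depends on recorded values. They were planned for about 5% missing, however, not for up to half of one arm stopping because of recovery. Choosing the main comparison day can be left to an analysis plan; collecting the data cannot.

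Several stronger readings are tempting and are not supported:

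- *All secondary measures stop at ICU exit.* Weaning at day 20, clinical events, adverse events and ECG continue.
- *The remaining T3 patients are sicker than the remaining placebo patients.* The figures 0.80 and 0.27 are each relative to that arm's own mean. Under a common-threshold shift the remaining T3 patients are less sick.
- *Patients leave the data soon after weaning.* The documents give no interval from weaning to ICU discharge.
- *COVID-19 testing ends at ICU exit.* Section 11 names no COVID-19 test even in the ICU. The gap is a missing schedule for everyone.
- *The echocardiography passages flatly contradict each other.* One gives a setting and the other a frequency in the ICU. Both can hold, but the ward schedule is unclear.

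**Conclusion.** The point holds in limited form. Dated recording of haemodynamic, gas, laboratory and inflammatory measures is tied to ICU stay. On the protocol's own rates, up to 50% of T3 and 15% of placebo patients could leave it by day 30, so late repeated measures comparisons condition on recovery.

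With deaths set aside the bias is against T3: about half of a true benefit under the latent-shift model, or 0.16 to 0.37 SD of apparent harm on an unaffected marker. Those sizes rest on assumed correlations, normal severity, the least sick leaving first, and all weaned patients having left. With deaths, neither size nor direction can be fixed from the documents.

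The primary endpoint and its power are untouched. This is a worthwhile, inexpensive improvement to secondary data, not a flaw in the main comparison.

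**What to change.** - In section 11, record routinely charted vital signs, oxygenation, and standard laboratory and inflammatory values on the same fixed study days (for example days 3, 7, 14, 21 and 30) in every patient still in hospital, whatever the ward and whether or not study drug has stopped.
- Make an early fixed day the main between-arm comparison for these measures, with later days descriptive and deaths reported alongside. That most survivors are still in the ICU on the chosen day is an assumption to check against site experience.
- Reconcile sections 5.2 and 11 on echocardiography.
- State the days on which COVID-19 positivity is read from available tests.

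The cost is extra CRF entries from ward charts for about 20 weaned patients (19.5 on the protocol's rates). No tests or echocardiograms beyond routine care are asked for. Recovery-driven loss is removed while patients remain in hospital; loss after discharge and through death remains.

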**12. ADVERSE EVENTS**

## Definitions

### Adverse event

Any untoward medical occurrence in a patient or clinical trial subject administered a medicinal product and which does not necessarily have a causal relationship with this treatment [Dir 2001/20/EC Art 2(m)].

An adverse event can therefore be any unfavourable and unintended sign (e.g. an abnormal laboratory finding), symptom, or disease temporally associated with the use of a medicinal product, whether or not considered related to the medicinal product.

### Adverse drug reaction (ADR)

A response to a medicinal product which is noxious and unintended [DIR 2001/83/EC Art 1(11)]1. Response in this context means that a causal relationship between a medicinal product and an adverse event is at least a reasonable possibility (see Annex IV, ICH-E2A Guideline).

Adverse reactions may arise from use of the product within or outside the terms of the marketing authorisation or from occupational exposure [DIR 2001/83/EC Art 101(1)]. Conditions of use outside the marketing authorisation include off-label use, overdose, misuse, abuse and medication errors.

(All AEs judged by either the reporting investigator or the sponsor as having a reasonable causal relationship to a drug).

1. The relationship between an AE and a drug is considered **Certain** when:

The AE occurs in a plausible time relation to the administration of the drug and cannot be explained by a concurrent disease or other drugs or chemicals. The response to withdrawal of the drug (dechallenge) should be clinically plausible. The event must be definitive pharmacologically or phenomenologically, using a satisfactory rechallenge procedure if necessary.

1. The relationship between an AE and a drug is considered **Probable** when:

The AE occurs in a reasonable time relation to the administration of the drug, it is unlikely to be attributed to a concurrent disease or other drugs or chemicals and it follows a clinically reasonable response on withdrawal (dechallenge). Rechallenge information (AE reappearance after drug reintroduction) is not required to fulfill this definition.

1. The relationship between an AE and a drug is considered **Possible** when:

The AE occurs in a reasonable time relation to the administration of the drug, but it could also be explained by a concurrent disease or other drugs or chemicals. Information on drug withdrawal (dechallenge) may be lacking or unclear.

- The relationship between an AE and a drug is considered **Unlikely** when:

a causal relationship cannot be definitively ruled out, but

- other drugs, chemicals or underlying disease provide plausible explanations

and/or

- the temporal relation to the administration of the drug makes a causal relation improbable.

**An AE is considered Not Related** to a drug in case of:

- existence of a clear alternative explanation, and/or

- unreasonable temporal relationship between Drug and Event, and/or

- non plausibility.

**An AE is considered Unassessable** when:

it cannot be judged, because the information is insufficient or contradictory and cannot be supplemented or verified.

**Intensity of an AE/ADR**

- Mild: does not interfere with routine activities; in case of laboratory tests, when there is a mild abnormality.
- Moderate: interferes with the routine activities; in case of laboratory tests, when there is a moderate abnormality.
- Severe: makes impossible to perform routine activities; in case of laboratory tests, when there is a significant abnormality.

An AE/ADR is considered **Unexpected** when its nature, severity or outcome is not consistent with the information included in the **Summary of Product Characteristics** (SPC).

